
**Figure 2 F2:**
[figure not shown]
The schematic diagram of acupuncture and sham acupuncture group. **(A)** Acupuncture group; **(B)** Sham acupuncture group.

**Figure 3 F3:**
[figure not shown]
The flow chart of physical training group. **(A)** Abdominal breathing; **(B)** Left and right-side leg rotation; **(C)** Stretch legs after stomach retraction; **(D)** Ventral flat training.

The trial must end when the following happened: (1) When severe adverse reactions occur on the patient during the trial; (2) When serious complications or deteriorations happen; (3) When the patient is asked to withdraw from the clinical study; (4) When the patient does not cooperate or accept any treatment with the treatment-personnel repeatedly explaining ineffective.

We gather the patients into a WeChat chatting group to answer their questions anytime to prevent the above situations. We try to cooperate and share any knowledge of DRA with our patients to contact them more fluently and smoothly. Furthermore, when the patient gets any other problems, we will have the treatment and record the changes in the patient's condition. During the trial, any other treatment on DRA is not allowed in case of being interfered with. If one happened, the patient must withdraw from the study.

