### Randomization and Binding

A total of 144 eligible patients were recruited and randomly assigned at a 1:1:1 ratio to receive acupuncture treatment or sham acupuncture treatment or be placed on a physical training. Central randomization, using an online or messaging system, was performed by the Brightech Magnsoft Data Services. The randomization sequence was generated in blocks of varying sizes and stratified by centers.

The acupuncture and sham acupuncture groups were blinded, while those in the physical training group were not. All clinical examinations were performed by [name] and [name] physiotherapists blinded to data collected through the questionnaire. Due to iodophor disinfection traces in the abdomen after electroacupuncture, the therapists knew the groups, so [name] performed electroacupuncture treatment after rehabilitation exercise first. All the therapists did not know the purpose of the experiment.

The acupuncture and sham acupuncture groups were blinded, while those in the physical training group were not. All clinical examinations were performed by [name] and [name], two physiotherapists blinded to data collected. Due to iodophor disinfection traces in the abdomen after electroacupuncture, the therapists knew the groups. So [name] performed electroacupuncture treatment after rehabilitation exercise first. Outcome assessors, data collectors, and statisticians did not know the purpose of the experiment and were blinded to the treatment allocation.

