### Intervention

Acupuncture group: the patient was placed in the supine position, exposing the abdomen, and acupoints RN12 (Zhongwan), RN10 (Xiawan), ST25 (Tianshu), GB26 (Dai Mai), RN6 (Qi Hai), and RN4 (Guanyuan) were selected. The selection of acupoints was based on the previous literature and clinical experience of DRA. The skin at the acupoints was routinely disinfected, and the disposable sterile acupuncture needles were used for vertical acupuncture of 25–40 mm, 30 min once/day, five times a week for 2 weeks (Figure 2A).Sham acupuncture group: non-penetrating sham acupuncture is performed on the same points as the treatment group on the abdomen. Streitberger placebo needles with blunt tips are used. When they are fixed on the skin through plastic rings, patients will feel a pricking sensation, simulating a skin puncture. However, instead of penetrating the skin, the needles retract up into the shaft when pressed against the skin. We will formulate and follow standardize step-by-step instructions and operations to use the same rituals in the acupuncture and sham acupuncture groups as far as possible, 30 min once/day, five times a week for 2 weeks (Figure 2B).Physical training group: (1) Abdominal breathing: supine position, lower limb hip, and knee flexion, foam bricks are clamped between the legs. the abdomen will be humped while inhaling and is forced to the navel while exhaling. Abdominal muscles and pelvic floor muscles are forced to contract at the same time, ten times a group for three groups. (2) Left and right-side leg rotation: buckling, supine, legs down to the right. inhale, abdominal bulge, expiratory when abdomen muscle contraction, to, make double leg down to the left (power is core abdominal muscles, legs, not too much), the therapist skill on the right side of the internal, external oblique muscle in patients with muscle contraction, the muscle belly line direction, the other patients on your knees. Apply some resistance according to the patient's strength of the force. Do it alternately, 10 times on each side. (3) Stretch legs after stomach retraction: Patients prone position, the abdominal pad is a soft pillow, inhale, abdominal bulge, expiratory when abdomen muscle contraction (imagine navel carried from pillow side), in turn, the waist, on the left side of the hips, on the left side of the thigh, to raise the left lower limb, the core in the waist, leg without over pressure, and avoid the contralateral compensatory, therapists place the fourth finger near the lumbar spine feeling the relaxation from torn muscle contraction. Alternating left and right, do 10 reps on each side. (4) Ventral flat training: the patient is in the right described position, elbow flexion support on the bed surface, hip extension, calf flexion and thigh 90 degrees, abdominal uplift when inhaling, abdominal muscles when exhaling, upper body, buttocks and left lower limb straight lift off the bed surface, left upper limb lift, upper arm against the head, ear sticking, maintain relaxation after 10 s. Core in the abdomen, other parts of the body cannot apply excessive force. Alternating left and right, do 10 reps on each side (Figure 3).

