### Primary Outcome

We consider the IRD as the primary outcome of DRA treatment (7). The same ultrasonic doctor will measure and evaluate before and after the treatment and after a 6-month follow-up.

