### Data Analysis

Based on Preliminary experiment results, we estimated that each of the three clinical researchers involved in the trial would recruit around 28 patients in 3 months. In order to retain most of the patients during follow-up, we gather the patients into a WeChat chatting group to answer their questions anytime. Moreover, actively cooperate with their appointment time. We expect the loss to follow-up to be below 10%.

Baseline characteristics and clinical outcomes are described based on the intention-to-treat population (*n* = 144). Continuous variables are presented as mean (SD), and categorical variables are described as number and percentage.

The principal analysis for primary and secondary outcomes will be a generalized linear model (GLM) including the intervention arm, the dependent variable's baseline score, and other variables imbalanced at baseline as covariates. The dependent variable will be the post-intervention score. The GLM does not need a normal distribution in the dependent variable. However, the distribution of the variables will be analyzed using de Shapiro- Wilk test to perform an adequate descriptive analysis. The choice of the link function will depend on the distribution of the variable.

Other variables will be added as confounders in the model as secondary sensitivity analyses. We will first fit separate models, including each confounder, one at a time. Those variables whose inclusion in the model changes the estimates' treatment effectiveness by at least 10% will be considered as confounders. As suggested in the CONSORT statement, decisions about confounders will not be based on *P*-value.

Missing data of withdrawn participants will be accommodated with multiple imputation procedures in Stata 25.0 software (Stata Corporation). All *P*-values were from 2-sided tests, and results were deemed statistically significant at *P* < 0.05.

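### Two of the plan's own procedures, an undivided patient chat group and iodophor marks on the scanned abdomen, put the claimed blinding at risk

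*Protocol article*

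**What the plan says.** **Chat group.** The Intervention section, in the text after the Figure 3 caption, says "We gather the patients into a WeChat chatting group to answer their questions anytime". The Data Analysis section repeats it as a means of keeping patients in follow-up: "we gather the patients into a WeChat chatting group to answer their questions anytime". Neither place says whether the arms are kept apart or whether patients may discuss their treatment.

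**Participant blinding.** The section on randomization and blinding states: "The acupuncture and sham acupuncture groups were blinded, while those in the physical training group were not".

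**Iodophor traces and assessor blinding.** The same section concedes: "Due to iodophor disinfection traces in the abdomen after electroacupuncture, the therapists knew the groups". The response is one of session order: the operator "performed electroacupuncture treatment after rehabilitation exercise first". It then claims: "Outcome assessors, data collectors, and statisticians did not know the purpose of the experiment and were blinded to the treatment allocation".

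**Primary outcome.** IRD is measured by ultrasound: "The same ultrasonic doctor will measure and evaluate before and after the treatment and after a 6-month follow-up". The Secondary Outcomes section places the ultrasound measurements at the umbilicus and above it, and grades linea alba tension from elastography colours.

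**Skin preparation.** For the acupuncture arm the Intervention section says "The skin at the acupoints was routinely disinfected". For the sham arm it names no disinfection, but the same abdominal points are used and the procedure is to copy the real one as closely as is feasible.

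**The concern.** The sham arm is there so that acupuncture can be compared with a control whose patients do not know their allocation. Most of the secondary and other outcomes are questionnaires completed by those patients (SF-36, SF-MPQ-2, LDQ, MDQ, EPDS-10, ICIQ-SF and others). A forum in which women with penetrating needles and women with retracting needles can compare notes works against that blinding.

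The second route touches the primary outcome. The article identifies a visible cue to allocation on the abdomen, deals with it for the exercise sessions only, and then declares blinded the person who scans that abdomen. If a reader of IRD or of the elastography grade can see who was needled, the blinding claim no longer supports the result. Neither the generalized linear model nor multiple imputation can remove such a bias afterwards.

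**Working it through.** The plan gives no figure for blinding, so the check sets its statements side by side. The only arithmetic is a count of women on each side of the visible cue.

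**Route 1: chat group**

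1. Claim: acupuncture and sham women are blinded; training-only women are not.
2. Procedure: the patients are gathered in a chat group, in the singular both times, with no separation by arm.
3. What could be compared: the Intervention section gives one arm needles inserted to 25–40 mm and the other blunt needles that retract without entering the skin. The safety section lists bleeding and needle blocking among the events to record, and these would not ordinarily be expected where the skin is not entered.
4. Which contrast: training-only women already know their arm, so only acupuncture versus sham has participant blinding to lose.
5. Which outcomes: mainly the self-reported ones. IRD is not reported by the patient.

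**Route 2: iodophor traces**

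1. The article itself says that the traces reveal the group to therapists.
2. Putting exercise before needling keeps fresh traces out of the exercise session. It does nothing about a scan that follows needling.
3. The scan is on the abdomen, where the needling points also lie.
4. By scan: before treatment, no needling has taken place, so there is no trace. After treatment, traces may be present if the scan closely follows a session; the interval is not stated. At 6 months, traces are not plausible. So at most 1 of 3 scans is exposed.
5. That scan matters most: Data Analysis makes the post-intervention score the dependent variable, read here as the end-of-treatment value.
6. By arm, with 48 planned per group:

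| Assumption on sham arm | Women with traces | Women without | Acupuncture vs training | Acupuncture vs sham |
|---|---|---|---|---|
| Swabbed as in acupuncture arm | 48 + 48 = 96 | 48 | exposed | not exposed |
| Not swabbed | 48 | 48 + 48 = 96 | exposed | exposed |

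Acupuncture versus training is exposed under both assumptions. It is the contrast in the Hypothesis section, and the one whose expected mean IRDs (1.43 and 2.09, a difference of 2.09 − 1.43 = 0.66) enter the sample size section.

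The session-order remedy also bounds the problem. Treatment is daily, five times a week, so doing exercise first hides the group only if traces are largely gone by the next session. On that premise, a scan on a later day would be at little risk and one straight after a session would be at real risk. The article does not say which is planned.

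**The case against.** The case on the other side is substantial, and much of it stands.

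- **A reader might infer that all 144 women share one forum.** That is the natural reading, but it is not stated. Separate groups by arm are not excluded, and the stated purpose is for staff to answer questions. This stands, so the point is the absence of any separation or posting rule where the procedure is described.
- **A reader might infer that blinding is broken.** The text shows routes by which it could fail, not that it fails. The article says that therapists learn the group from the traces; it does not say this of the ultrasound doctor. This stands.
- **A reader might infer cross-arm contamination through swapped exercises or other treatments.** The documents do not support this. All three arms receive the physical training, and the Intervention section forbids other treatment for the condition and requires withdrawal if it occurs.
- **The chat barely touches the stated hypothesis.** Correct: acupuncture versus training has no participant blinding to lose.
- **A condensed article may leave scan timing and skin cleaning to the full protocol.** This is fair as to the details. It does not dispose of the point, because the article raises the trace problem itself, offers a remedy that stops short of the primary-outcome assessor, and still asserts that the assessor is blinded.

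**Conclusion.** The point holds as a risk to blinding created by the plan's own procedures.

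The chat group, as described, leaves the acupuncture-versus-sham participant blinding unprotected, chiefly for patient-reported outcomes. This assumes that women from both needle arms are in the same group and can post to each other.

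The iodophor remedy leaves the assessor's blinding unsecured at the post-treatment scan, for the primary outcome and the hypothesised contrast. This assumes a scan soon enough after a session for traces to remain, without cleaning. A split of 96 women against 48 by visible traces should not be quoted as fact: it requires the sham arm to be swabbed, and otherwise the 48 stained women are the acupuncture arm alone.

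The documents give nothing from which to derive the size or direction of any resulting bias. The case for acting is that such bias cannot be repaired in analysis and is cheap to prevent.

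**What to change.** 1. Replace the group chat with one-to-one messages, or a broadcast-only channel, from the study account, with no posting between patients.
2. Before each post-treatment scan, have existing staff other than the ultrasound doctor clean the abdomen, or apply the same skin preparation at the same points in all three arms.
3. Do not scan straight after a session, and state the interval between the last session and the scan.
4. In the section on randomization and blinding, say that the ultrasound doctor's blinding is secured by these steps, and state whether the sham arm is swabbed.

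Cost: slightly more staff messaging, the loss of peer support in the chat, and about a minute of skin preparation per scan. Sample size and analysis are unaffected.

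### Ending study participation on other DRA treatment, deterioration or non-cooperation creates avoidable missing IRD and leaves the intention-to-treat result for these women dependent on imputation

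*Protocol article*

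**What the plan says.** The Intervention section of the protocol article (text after Figure 3) lists events at which the trial ends for a patient. They include severe adverse reactions, "When serious complications or deteriorations happen", and non-cooperation: "When the patient does not cooperate or accept any treatment with the treatment-personnel repeatedly explaining ineffective". It then prohibits other care for the condition: "During the trial, any other treatment on DRA is not allowed in case of being interfered with". The consequence follows directly: "If one happened, the patient must withdraw from the study". The words refer to the study, not only to study treatment, and no period shorter than the trial is named.

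Primary Outcome has IRD measured before treatment, after treatment and after 6 months of follow-up. Treatment lasts 2 weeks.

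Data Analysis states: "Baseline characteristics and clinical outcomes are described based on the intention-to-treat population", with n = 144. It adds: "Missing data of withdrawn participants will be accommodated with multiple imputation procedures". The principal model is a generalised linear model of the post-intervention score on arm, baseline score and covariates imbalanced at baseline. The only sensitivity analyses described there add confounders.

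**The concern.** Stopping a treatment and stopping measurement are different events, and the withdrawal rule merges them. A woman can deteriorate, refuse sessions or obtain treatment elsewhere and still attend an ultrasound. If she must leave the study, her later IRD is missing because the plan says so, not because it could not be obtained.

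The triggers may also be related to the outcome. Deterioration is the plainest case. Use of other DRA treatment could be another, since a woman with persistent separation has a reason to look for it. The triggers may act differently by arm, because Randomization and Binding says that the physical training group is not blinded while the two needle groups are.

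Multiple imputation in its usual form assumes that missingness is explained by the data already observed. A woman who leaves early because of how she fared after baseline may have no later IRD to inform the model. No later analysis can recover a measurement that was never taken, so the choice has to be made before data are lost.

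**Working it through.** **1. What happens to a withdrawn woman**

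- Intervention: other DRA treatment leads to withdrawal from the study; deterioration, severe adverse reactions or non-cooperation end the trial for her.
- Data Analysis: she remains among the 144, and her missing data are imputed.
- Neither section says that her IRD is still measured. Data Analysis expects withdrawal to produce missing data.

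She leaves the observed data, not the analysis set.

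**2. Which time point is exposed**

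The ban runs during the trial, which is 2 weeks of treatment plus half a year of follow-up. Most of that time lies after the end-of-treatment scan. A woman who takes other treatment during follow-up already has that scan, so only her 6-month value is lost. Early leavers lose both.

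**3. The plan's own sample size**

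Inputs from Sample Size: effect size 0.313249 (read as Cohen's f for three groups), two-sided alpha 0.05, power 90%, 43 per group, 10% loss. A one-way ANOVA F test gives power 0.893 at 43 per group, and 45 is the first n to reach 0.90. The stated 43 therefore reproduces closely. Then 43/0.9 = 47.8, rounded up to 48, and 3 x 48 = 144. This point does not change the sample size.

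**4. Implied SD**

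The article gives no SD, so it is derived here and is an assumption. The means are 2.09 (training) and 1.43 (acupuncture plus training), a difference of 0.66, taken as cm. SD = (standard deviation of the three group means)/f.

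- Third mean midway: 0.2694/0.313249 = 0.86
- Third mean equal to either arm: 0.3111/0.313249 = 0.99

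**5. Illustration at the end of treatment**

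Assume that a share p of one arm leaves before the end-of-treatment scan and that imputation recovers nothing.

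- Leavers average 1 SD worse than their arm (p = 0.10): shift = SD x p/(1 - p) = 0.111 x SD, or 0.10-0.11 cm.
- Leavers are the worst 10%: shift = SD x phi(z)/(1 - p), with z = 1.2816 and phi(z) = 0.1755, so 0.195 x SD, or 0.17-0.19 cm. Against 0.66 this is 25-29%.

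Effect on the observed difference when the women with the largest IRD leave:

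| Lost from training | Lost from acupuncture | Observed difference (planned 0.66) |
|---|---|---|
| 10% | 0% | 0.47-0.49 |
| 10% | 5% | 0.57-0.59 |
| 20% | 10% | 0.51-0.53 |
| 10% | 10% | 0.66 |
| 0% | 10% | 0.83-0.85 (0.66 + 0.17 to 0.66 + 0.19) |

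The direction depends on which arm loses more. Loss concentrated in training shrinks the difference; loss concentrated in acupuncture inflates it.

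**6. What cannot be computed**

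The article gives no planned difference at 6 months, no correlation between baseline and later IRD, and no withdrawal rate by reason. The bias at 6 months, where the rule has most room to act, cannot be sized.

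**The case against.** The strongest reply is that the plan foresees withdrawal and deals with it. All 144 women stay in the analysis population, and a recognised method is named for their missing data. A reader might infer that the withdrawal rule contradicts the intention-to-treat analysis, or that treatment failures are removed from it. The documents do not support either reading, for the reason given in step 1.

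The article also does not say outright that scans stop at withdrawal. Its SPIRIT checklist answers yes to the item on outcome data for participants who discontinue or deviate, and the full protocol may hold the detail. This has some weight, but a ticked checklist does not show the content, withdrawal from the study reads naturally as the end of follow-up, and the article itself expects missing data from these women.

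The imputation model is not given. Baseline IRD, and for later leavers the end-of-treatment IRD, could serve as predictors and recover part of any shift. The Abbreviations list pattern mixture models, although the text never applies one. So it cannot be said that imputation must fail, only that it may.

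The illustration is close to a worst case. It puts the whole anticipated 10% loss, for any reason, into outcome-related loss from one arm, and gives imputation no credit. It is set against an after-treatment difference that withdrawals during follow-up cannot shift. All of this stands, and the figures should not be read as an expected bias.

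It is also tempting to say that leavers will mainly be non-responders, or that the training arm will lose more of them. The documents establish only that the training arm is unblinded; the rest is inference.

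**Conclusion.** The point holds in a limited form. Followed as written, the rule turns other DRA treatment, deterioration and non-cooperation into avoidable missing IRD, for reasons that may depend on outcome and on arm. The intention-to-treat result for these women then depends on imputation, chiefly at 6 months. There is no contradiction with the intention-to-treat population.

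The size and direction of bias are unknown. The 0.17-0.19 cm shift is an upper-end illustration. It rests on an SD of 0.86-0.99 that the article does not state, on the worst 10% leaving one arm before the end-of-treatment scan, and on no recovery by imputation. With equal loss of this kind in both arms the difference stays at 0.66 cm. The case for acting does not rest on that figure: the missing data are created by the plan and can largely be avoided.

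**What to change.** Reconcile the withdrawal text in Intervention with Data Analysis by separating the end of study treatment from the end of outcome collection:

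- Keep the scheduled end-of-treatment and 6-month assessments (ultrasound and questionnaires) for every randomised woman who has not withdrawn consent, whatever treatment she received.
- Record any other DRA treatment with its date.
- Analyse by randomised arm.
- Use multiple imputation only for visits that are truly missing. Add a delta-shifted sensitivity analysis, in which imputed IRD is made progressively worse, with the shift allowed to differ by arm.

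The cost is a short amendment, a few already scheduled visits kept for women who would otherwise be lost, and a little more analysis. The change concerns data collection and analysis only. The clinical rules on stopping treatment and on other treatment are left to the investigators.
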